### Seizure-related outcomes

Seizure-related outcomes will include treatment responder rates (participants with ≥25%, ≥50%, ≥75%, and 100% reduction in seizure frequency from baseline). The proportion of participants who experience a worsening, no change, or improvement in seizure frequency will be evaluated, along with the change in the number of seizure-free days from baseline. Change in overall severity of seizure symptoms will be evaluated by caregivers/participants using the CareGI-S/PGI-S scale and by clinicians using the CGI-S scale.

Participant retention at weeks 13, 26, and 52 following the initiation of treatment will be evaluated.

### Safety and tolerability

Safety and tolerability assessments will include incidence and severity of treatment-emergent adverse events (AEs), incidence of serious AEs, discontinuations because of AEs, number of inpatient hospitalizations due to epilepsy, abnormal clinical laboratory parameters, suicidal ideation, and behavior risk monitoring throughout the study duration. At the end of the first treatment period, caregivers will be given a short questionnaire of approximately three items to determine reasons for remaining on or discontinuing CBD treatment.

### Statistical analysis

EpiCom is an exploratory study, so no formal statistical hypothesis will be tested. Ranking is not assigned to the study endpoints; therefore, no hierarchical testing strategy or other multiplicity adjustments will be considered. Given that the study is not controlled, no direct causal attribution of any observed association to CBD treatment will be made based on study findings. The study is not designed to distinguish whether improvements in TAND outcomes are due to CBD treatment or if they are the result of seizure reduction. A modelling approach will be used to explore the extent to which the observed associations of CBD treatment with TAND endpoints is associated with the change in seizure frequency during follow-up. Its marginal/causal effects may be further investigated with an exploratory mediation analysis [64].

Outcomes will be reported using standard descriptive statistics for continuous variables, including 95% CIs for the mean (including SD) or median (including the first and third quartiles, and the minimum and maximum values) change. Counts and percentages will be reported along with the 95% CI of the rate. Statistics will be presented overall and by age, where applicable. If provided, *P* values will be declared as nominal. An intermediate analysis at week 26 will be performed to describe any early trends.

A generalized linear mixed model (GLMM) will be used to evaluate the significant change from baseline to week 26 in effectiveness endpoints, adjusted by the assessment at baseline and age at baseline. During the second treatment period, summary statistics for endpoints may be computed for and between the CBD treatment and SoC arms. At week 52, a GLMM will be used to describe the association of treatment with change from baseline in effectiveness endpoints, adjusted by assessment at baseline, and a propensity score calculated based on age at baseline, sex, percentage change from baseline at week 26 in seizure frequency, 28-day average seizure-free days at week 26, and the number of concomitant ASMs. Least-squares means of the treatment effect (CBD vs SoC), two-tailed 95% CI and the unadjusted *P* values will be generated if at least 25% of the participants reaching the 26-week interim review will opt for SoC treatment in the second treatment period.

All participants who sign the informed consent form and take ≥1 dose of CBD will be included in analysis of safety endpoints (safety analysis set). Participants who, in addition to the above criteria, also complete ≥1 postbaseline assessment will be included in the effectiveness endpoints analysis (full analysis set). The raw data captured electronically will be converted to analysis datasets according to the Clinical Data Interchange Standards Consortium standards and principles. Data management and analyses will be performed using SAS version 9.4 (or higher) of the SAS Institute.

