ASR^a^ [36] The ASR is a participant-reported version of the ABCL	Change from baseline at weeks 26 and 52	ASR is validated in participants aged 18–59 years; however, in the current study, it will be used for participants aged 18–65 years	15–20 min
PROMIS [38–40] Developed by the NIH as a collection of standardized outcome assessments for use in clinical studies This study will incorporate caregiver-assessed short-form PROMIS scales pertaining to the following domains: emotional distress (anger/irritability, anxiety), cognition, positive affect, and sleep disturbance	Change from baseline to weeks 26 and 52 in PROMIS domains	Can be used for children and adults Widely used and validated in large clinical trials [40]	≈5 min/questionnaire
BRIEF [41,42] A set of questionnaires to evaluate executive function from multiple perspectives Theoretically and statistically derived scales measure behavioral aspects such as the ability to control impulses, move freely between situations, modulate responses, anticipate future events, and monitor how an individual’s behavior impacts others BRIEF questionnaire will be completed by the caregiver	Change from baseline at week 26	BRIEF-P: validated for use in participants aged 2–5 years [43] BRIEF2: validated for use in individuals aged 6–18 years [44] BRIEF-A: validated for use in individuals aged >18 years [45] Questionnaires have been used in epilepsy studies and can be used with children who have developmental or acquired neurologic conditions such as learning disabilities, attention disorders, traumatic brain injury, lead exposure, pervasive developmental disorders, depression, and other developmental, neurologic, psychiatric, and medical conditions	10–15 min/ questionnaire
Abbreviated CSHQ [46,47] A caregiver-reported tool used to assess sleep habits and possible difficulties with sleep during the past week Includes items regarding bedtime habits, sleep behaviors, waking through the night, and morning wake-up	Change from baseline at week 26	Well-established sleep measure Validated in children 4–10 years and 2.5–5 years; has been used in children up to 12 years of age [48]	≈10 min

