### Sample size

Planned enrollment is for 75 participants, such that 60 participants may be evaluable at the 26-week interim review (assuming a 20% withdrawal rate during the first treatment period). Participants will be considered evaluable for a given endpoint if they complete the endpoint assessment at baseline and at the 26-week interim review. Although not required, the study will attempt to enroll approximately 25 adult participants.

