## Discussion

There is an increasing focus on incorporation of “patient experience data” into decision-making for clinical trials and drug development process [63]. Including patient experience information in trial design gives patients a voice and allows for evaluation of endpoints that are of importance to them and their families. The EpiCom study was designed to increase the potential for efficient study execution, data dissemination, and impact on patient care.

In addition to keeping patient and caregiver input at the center of the study design process, EpiCom aims to reduce the burden associated with trial participation by implementing a hybrid decentralized clinical trial (DCT) approach, in which participants will have the choice to attend the clinical trial site, conduct the assessments at home, or both. The DCT strategy allows for clinical trial activities to be conducted at locations other than traditional clinical trial sites, such as the patients’ homes or other locations remote from the clinical trial site (e.g., access to video call visits, home phlebotomy for blood collection, and home delivery of study drug), as well as the use of digital health technologies (e.g., access to assessment tools via their own mobile device or directly on the web). Using the DCT approach, more participants can access the investigational treatment, which in turn can support inclusion of a greater diversity of patient populations and increase efficiency by reducing the burden on caregivers and enhancing engagement among participants, thereby increasing patient recruitment and retention [65].

Highly purified CBD (Epidiolex^®^) is already an approved treatment for seizures associated with TSC in many countries; therefore, because of ethical considerations and based on advice from PAGs, EpiCom was designed as an open-label, single-arm trial to ensure that CBD is available to all eligible participants. The assessment tools were selected primarily on the basis of what the advisory panel members considered the most effective method for measuring outcomes that are of value to the participants of the trial. Other considerations were the validation status of the tools, their previous use in TSC or similar studies, and the time needed to complete the assessments and their complexity.

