A limitation of the study is lack of a specific statistical strategy to measure the response bias and bias recalibration (change in response bias between two time periods). To mitigate this, the study’s statistical analysis uses a GLMM on repeated endpoints to quantify the magnitude of the dimension scale score’s difference from the baseline. The model accounts for within-subject correlation, confounding factors, and baseline assessments to reduce variability and the presence of reporting bias. Additionally, caregivers may have completely different views on the “severity-rating” of certain behaviors experienced. Such a subjective symptom under any circumstance would be challenging to standardize. To increase data accuracy, consistency and impartiality, several different questionnaires were included in the protocol to assess changes in the same nonseizure outcomes, including the patient’s most problematic behavioral symptom from clinician and caregiver perspectives. Also, to reduce intra- and interparticipant variability, training materials such as a behavioral severity discussion guide were designed in collaboration with PAGs to support discussions between study investigators and caregivers (who will be administering the assessments), to align on severity grading of the participant’s behavioral symptoms prior to formal consent and screening procedures.

We are continuing to work in partnership with an engaged and integrated patient/caregiver-HCP community that is enthusiastic and invested in the support of the clinical study delivery and interpretation. The use of the collaborative approach described here could serve as a blueprint to inform future studies evaluating potential pharmacotherapies for neuropsychiatric outcomes in TSC and similar populations. This study began enrolling participants from the US in June 2023. The UK, Canada, and Poland will soon follow. Last patient in is expected in the first quarter of 2025 with database lock in first quarter of 2026.

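### Adjusting the single-arm week-26 mean change for baseline adds no precision, and with the usual model-based standard error it makes the interval too narrow

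*Protocol article*

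**What the plan says.** In the Protocol article, Statistical analysis, the week-26 model is to "evaluate the significant change from baseline to week 26 in effectiveness endpoints, adjusted by the assessment at baseline and age at baseline". The Discussion explains that design: "EpiCom was designed as an open-label, single-arm trial to ensure that CBD is available to all eligible participants". No between-group contrast therefore exists at week 26.

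The limitations paragraph of the Discussion says that the analysis "uses a GLMM on repeated endpoints to quantify the magnitude of the dimension scale score’s difference from the baseline". It adds: "The model accounts for within-subject correlation, confounding factors, and baseline assessments to reduce variability and the presence of reporting bias". The baseline adjustment is thus a stated choice with a stated reason, not a detail left open.

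Statistical analysis also says that the study is exploratory, that any P values are nominal, and that descriptive 95% intervals for the mean or median change will be reported. It names least-squares means and a two-tailed 95% interval only for the week-52 comparison of CBD with standard of care. For week 26 it gives neither the point at which the adjusted mean is evaluated nor the standard-error method.

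**The concern.** In a trial with two arms, adjusting for baseline removes noise from the difference between arms. That reasoning does not carry over to one group's mean change. Here the baseline score is itself half of the change, and its sample mean varies from sample to sample. A model that conditions on baseline treats that mean as a known constant. The estimate stays the same, and only the reported standard error shrinks.

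At stake is the nominal error rate of the model that the plan uses to judge whether scores changed. A reader could also meet two intervals for the same mean change, with the narrower one coming from the model that looks more rigorous.

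**Working it through.** **Inputs from the article.** Sample size section: "Planned enrollment is for 75 participants, such that 60 participants may be evaluable at the 26-week interim review". The allowance for early loss is one in five. The plan's own figure reproduces: 60 / (1 − 0.20) = 75. The checks below use n = 60 unless stated.

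**Assumptions, because the article is silent.** Continuous score with identity link; adjusted mean evaluated at the observed mean baseline; model-based standard error; equal SD *s* at baseline and week 26; correlation ρ shown as a range.

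**Step 1: the estimate.** Regress change D on centred baseline X and centred age. The intercept is the raw mean change, so adjustment does not alter the estimate.

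**Step 2: the variances.**
- Correct variance of the mean change: Var(D)/n = 2s²(1 − ρ)/n.
- Variance reported by the model: residual variance/n = s²(1 − ρ²)/n.
- Omitted part: (slope of D on X)² × Var(X)/n = (1 − ρ)²s²/n. Check: 2(1 − ρ) − (1 − ρ²) = (1 − ρ)².
- Ratio of reported to correct standard error: √[(1 + ρ)/2].

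**Step 3: the numbers.** The simulation has n = 60, baseline and an unrelated age as covariates, a true mean change of zero, and 40,000 samples per row.

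| ρ | SE ratio | Analytic coverage | Simulated coverage, adjusted model |
|---|---|---|---|
| 0.3 | 0.806 | 88.6% | 88.8% |
| 0.5 | 0.866 | 91.0% | 91.1% |
| 0.7 | 0.922 | 92.9% | 93.0% |
| 0.8 | 0.949 | 93.7% | 93.7% |

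In the same samples the paired interval covered 94.9% to 95.0%. At ρ = 0.5 (with s = 1) the true standard error of the estimate was 0.130 and the average reported one was 0.111.

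**Step 4: does a repeated-change model cure it?** With weeks 13 and 26 both modelled as changes, unstructured covariance and the baseline covariate kept, the two-sided error at week 26 was 11.0%, 8.4% and 7.3% for ρ = 0.3, 0.5 and 0.7. It does not.

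**Step 5: when is it smaller?** With the baseline cut to its upper half, the error was 7.3%, 6.0% and 5.6% for ρ = 0.3, 0.5 and 0.7. With a week-26 SD 1.3 times the baseline SD and ρ = 0.5 it was 6.2%. It disappears when the slope of the week-26 score on baseline is 1.

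**Step 6: does the remedy hold?** With 75 enrolled, roughly 20% to 25% dropout depending on baseline, and baseline kept as a response, the estimate was unbiased and coverage was about 95% for ρ = 0.3, 0.5 and 0.7. Under that same dropout, the paired change in completers was biased by 0.10, 0.07 and 0.04 SD.

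**The case against.** The strongest reply is that the faulty interval is inferred. The article does not say how the week-26 standard error is formed, and an analysis plan could add the missing variance without contradicting it. That stands as a condition on the size. It does not rescue the stated reason for adjusting, because no variability of the mean change is reduced.

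Inference conditional on the observed baselines is valid on its own terms. It does not, however, answer whether the mean changed in the population from which the participants come.

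The study is exploratory, P values are nominal, and an unadjusted descriptive interval is already planned. This lowers the consequence, but labelling a P value nominal does not correct the coverage of a 95% interval.

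Eligibility restricts some baselines: the most problematic behavior score must be at least 6, and the required moderate or severe CareGI-S rating may narrow related scales. For those scales the smaller figures in step 5 are the better guide.

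Two stronger readings are tempting, and the article supports neither.
- Table 1 lists BRIEF, CSHQ, PSQI, PedsQL and PedsQL FIM for change at week 26 only (for BRIEF and CSHQ, "Change from baseline at week 26"). A reader might infer that withdrawals contribute nothing on these instruments. The Fig 1 footnote asks participants who withdraw before week 26 to complete the assessments of that visit, so only those without such a value are lost.
- A reader might also infer that the statement "The model accounts for within-subject correlation" is false for these instruments. The preceding sentence in the Discussion ties the model to repeated endpoints, so the article does not make that claim for instruments with one post-baseline visit.

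**Conclusion.** The point holds in a limited form. Adjusting the single-arm mean change for baseline adds no precision, and the reason given for it in the Discussion is mistaken for this estimate. If the week-26 inference uses the usual adjusted mean with a model-based standard error, that standard error is about 19% too small at ρ = 0.3 and about 5% too small at ρ = 0.8, with coverage of about 89% and 94%. These figures assume equal SDs and an untruncated baseline. The loss is smaller with truncation or a larger week-26 SD.

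The effect on conclusions is moderate, and the plan should be changed before analysis. The planned descriptive interval is not affected. The week-52 comparison of CBD with standard of care is a between-group contrast and is not affected in this way.

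**What to change.** For the week-26 mean change, take the 95% interval and the nominal P value from a repeated-measures model with the baseline value in the response vector, visit as a factor, unstructured within-participant covariance and no baseline covariate. Report the week-26 minus baseline contrast. The unadjusted paired change is a simpler alternative. The repeated-measures model is preferable with dropout because it keeps participants who have only a baseline value.

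Show age by subgroup rather than as a covariate in this contrast. Centring age at its sample mean has the same defect wherever change varies with age, usually to a smaller degree.

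In the Discussion, drop the statement that baseline adjustment reduces variability as far as it concerns the week-26 mean change.

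The cost is one model statement and a few words of text. Relative to the adjusted model, intervals widen by a factor of 1/0.949 = 1.05 at ρ = 0.8 to 1/0.806 = 1.24 at ρ = 0.3, that is, by about 5% to 24%.

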**Fig 3 pone.0324648.g003:**
[figure not shown]
Study schema. *Participants who decide to discontinue CBD after the 26-week interim review visit but remain on study will form the SoC treatment arm. These participants will taper off CBD and complete a safety follow-up. ^†^Participants who decide to discontinue CBD after the 52-week final review visit will taper off CBD and complete a safety follow-up. For participants who wish to remain on CBD after the study, the 52-week final review visit is the last study visit. CBD: cannabidiol; SoC: standard of care.

During the first 26 weeks of treatment, participants will receive open-label CBD treatment in addition to the SoC. This treatment period consists of the following two phases: a 4-week titration period, during which the CBD dose will be titrated up to the participant’s optimal maximum dose (study site staff will train the participants or caregivers on how to dose and titrate CBD), and a 22-week maintenance period, during which the participants will maintain their optimal dose of CBD. Following a review after the first 26 weeks of treatment, participants will have the option to either continue adjunctive CBD treatment for another 26 weeks or discontinue CBD while maintaining their SoC treatment. Participants who choose to discontinue CBD after a 26-week interim review visit will be gradually withdrawn over a 10-day taper period and complete an end-of-taper visit and a follow-up safety assessment.

Participants who choose to continue treatment with CBD will maintain their dose for the remainder of treatment period 2, until the 52-week final review visit, which will also be the last study visit. Participants who do not continue CBD (outside of the study) after the 52-week final visit will undergo a 10-day taper period and complete an end-of-taper visit and a follow-up safety assessment. Participants will have the option to complete all study visits either at the study site or virtually (e.g., via telehealth or videoconference).

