**TAND Outcomes**			
ABC [26,27] A caregiver-reported tool that allows for assessments of problematic behavior in children and adults with developmental disabilities Caregivers will rate the participant’s specific symptoms across the following subscales: irritability, social withdrawal, stereotypic behavior, hyperactive noncompliance, and inappropriate speech	Change from baseline at weeks 13, 26, and 52	Can be used for children and adults Used for assessment in diseases with behavioral problems, including ASD, Down syndrome, and fragile X syndrome [26,28,29] Widely used for evaluating treatment outcomes in autism [30,31,32]	10–15 min
TAND-SQ [19,20] A checklist completed by caregivers or adults^a^ with TSC for assessment of symptoms across TAND-related domains (i.e., neuropsychiatric, cognitive, and behavioral symptoms, psychosocial impact, and overall burden) that can be tracked over time The single most problematic behavior on TAND-SQ for each participant will be identified by the caregiver and the change over time in that behavior will be assessed using an 11-point Likert-type scale Changes in the TAND clusters (scholastic, neuropsychological, ASD-like, dysregulated behavior, overactive/impulsive, mood/anxiety, eat/sleep) and overall NRS TAND-related symptoms will also be evaluated in the study	Change from baseline at weeks 13, 26, and 52	Under validation as part of the TANDem project [21]	20–30 min
CBCL [33,34]/ABCL [35,36] Caregiver-reported questionnaires that examine internalizing behaviors (e.g., depression and anxiety), externalizing behaviors (e.g., aggression), stress, obsessive-compulsive behaviors, and “sluggish cognitive tempo” These questionnaires allow for an assessment of the participant’s behaviors on a 3-point Likert scale	Change from baseline at weeks 26 and 52	CBCL, ABCL, and ASR are components of ASEBA, a widely used and validated measure to assess behavioral, emotional, and social problems and adaptive functioning in individuals of all ages [37] Versions of the CBCL are validated in participants aged 1.5–5 years and 6–18 years CBCL was found to not be as effective as the TAND checklist in detecting neuropsychiatric and psychopathological problems associated with TSC [34] ABCL is validated in participants aged 18–59 years; however, in the current study, it will be used for participants aged 18–65 years	15–20 min

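### The week-52 CBD versus SoC model compares self-chosen groups and adjusts for week-26 seizure response but not week-26 behaviour, so its behavioural contrasts are biased if behavioural response influences the choice

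*Protocol article*

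**What the plan says.** **How the groups arise.** Everyone is assigned CBD in treatment period 1. After the week-26 review, "participants will have the option to either continue adjunctive CBD treatment for another 26 weeks or discontinue CBD while maintaining their SoC treatment" (Protocol article, Study design, text with Fig 3). The Fig 3 legend defines the comparator: "Participants who decide to discontinue CBD after the 26-week interim review visit but remain on study will form the SoC treatment arm".

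**The week-52 model.** The Statistical analysis section uses a GLMM to "describe the association of treatment with change from baseline in effectiveness endpoints, adjusted by assessment at baseline". The model further adjusts for "a propensity score calculated based on age at baseline, sex, percentage change from baseline at week 26 in seizure frequency". The two remaining components of that score are seizure-free days per 28 days at week 26 and how many ASMs the participant takes. If at least 25% of those reaching the interim review choose SoC, least-squares means, a two-tailed 95% CI and an unadjusted P value are produced. The CBD versus SoC contrast is there called a treatment effect.

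**What is measured at week 26.** Table 1 gives ABC and TAND-SQ as "Change from baseline at weeks 13, 26, and 52". CBCL/ABCL, ASR and PROMIS are assessed at weeks 26 and 52, and the global severity scales at weeks 4, 13, 26 and 52. At the end of period 1, "caregivers will be given a short questionnaire of approximately three items to determine reasons for remaining on or discontinuing CBD treatment" (Safety and tolerability).

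**Qualifications.** The Statistical analysis section states that the study is exploratory, that P values are nominal and that no direct causal attribution to CBD will be made. The Discussion, however, says that the model takes account of confounding factors.

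**The concern.** The two arms do not exist until week 26, and participants sort themselves into them after seeing how 26 weeks of CBD went. The score accepts that week-26 response can influence the choice, because it contains two week-26 seizure measures. It has no counterpart for behaviour, although moderate or severe behavioural problems are an entry criterion and behaviour is the study's focus.

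If families whose child's behaviour improved are more likely to stay, the CBD group starts period 2 ahead. Part of that lead persists to week 52 and appears in the CBD versus SoC contrast, even if continuing CBD adds nothing. Adjusting for the baseline score cannot remove a difference that arises after baseline. Seizure response is only a partial proxy: the Introduction reports, from the expanded access cohort, behavioural gains also in individuals without seizure reduction.

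At stake is the plan's only modelled comparison between CBD and SoC, in a study whose results are meant to inform later trials.

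**Working it through.** **1. The plan's own figures.** Enrolment: 60 / (1 − 0.20) = 75, as stated under Sample size. The reporting trigger, applied to 60 participants, is 0.25 × 60 = 15 on SoC. The article gives no SD, effect size or selection rate, so nothing else can be reproduced.

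**2. Structure of the bias.** Suppose there is no period-2 effect and the week-52 score depends on the week-26 score with slope β. Let Δ be the CBD minus SoC difference in the week-26 score that remains after adjustment for baseline and the propensity score. Then

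false difference ≈ β × Δ.

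It is zero if Δ = 0 (behaviour does not drive the choice), and its sign follows the sign of Δ.

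**3. Simulation under no period-2 effect.** Assumptions, none of them from the article: correlation of 0.3 between behavioural and seizure response, and persistence from week 26 to week 52 of 0.5 or 0.7. There are 60 participants with 25% on SoC. The analysis is a linear model of week-52 change from baseline on arm, baseline value and propensity score. The table uses all five listed covariates, with about 1,190 runs per cell.

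| Odds ratio of staying per SD of improvement | False CBD benefit (SD) | Nominal P<0.05 |
|---|---|---|
| 1 | 0 | 4–5% |
| 1.5 | 0.14–0.18 | 7–8% |
| 2 | 0.22–0.32 | 10–18% |
| 4 | 0.39–0.53 | 23–42% |

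A separate simulation with a simpler score (seizure change and age, 2,000 runs per cell) gives 0.13–0.20 SD and 8–11% at odds ratio 1.5, and 0.23–0.56 SD and 11–48% across odds ratios 2 to 4. Together the two span 0.13 to 0.56 SD and 7% to 48%.

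**4. Sensitivity.**
- *Reverse selection* (odds ratio 0.5): 0.27 SD against CBD.
- *Behaviour and seizure response strongly correlated* (0.7 instead of 0.3, odds ratio 2): the bias falls from 0.27 to 0.15 SD, and rejection from 13% to 7%.
- *A different data model*, in which change is unrelated to the baseline score, seizure response also drives the choice, and selection log-odds are 0.5, 1.0 and 1.5 per SD (odds ratios 1.65, 2.72 and 4.48): with persistence 0.7 and correlation 0.3, the bias is 0.30, 0.52 and 0.70 SD, and rejection 15%, 37% and 62%. In this model baseline adjustment removes nothing, which is one reason the figures are larger.
- *Check of β × Δ* in that last model at log-odds 1.0: biases of 0.383, 0.524 and 0.690 SD at persistence 0.5, 0.7 and 0.9 give Δ = 0.383/0.5 = 0.77, 0.524/0.7 = 0.75 and 0.690/0.9 = 0.77. Δ is stable, as the formula requires.

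**5. With the week-26 value added.** In the five-covariate simulation the bias is within about 0.01 SD and rejection is 4–7%. In the different data model, with week-26 behaviour added to score and model, the bias lies between −0.01 and +0.03 SD and rejection is about 4–7%. In all of these the choice depended on the measured week-26 change, so this near-complete removal is the best case.

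**6. The choice of change score.** Write the corrected model as

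y52 − y0 = a + b·arm + c·y0 + d·y26 + error.

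Adding y0 − y26 to both sides gives

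y52 − y26 = a + b·arm + (c+1)·y0 + (d−1)·y26 + error.

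The arm coefficient b is unchanged, and the same holds for y52 alone. Numerically the three agree to within 1e-13. The defect is the missing covariate, not the change from baseline as such.

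**The case against.** **Exploratory status.** No hypothesis is tested, P values are nominal, causal attribution is disclaimed, and the contrast is produced only if at least a quarter choose SoC. The baseline-to-week-26 analysis is untouched. All of this stands and lowers the severity. It does not correct the estimate, which is still printed as a treatment effect with a CI and P value.

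**Direction.** A reader might infer that the plan creates a false CBD advantage. The documents do not support that as a certainty. They contain no data on who stays, the reasons are collected only at week 26, and CBD is started for seizures, whose response the score covers. That improvers stay is plausible but is an inference.

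**Scope.** A reader might take every effectiveness endpoint to be affected. Seizure endpoints already have their week-26 status in the score. BRIEF, CSHQ, PSQI, PedsQL and PedsQL FIM have no week-52 endpoint.

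**Change from baseline and tolerability.** A reader might treat the change-from-baseline outcome as a second error; step 6 shows that it is not one once both values are covariates. Tolerability is also absent from the score and could matter, but its influence has not been quantified here.

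**Repeated-measures model.** The Discussion describes a GLMM on repeated endpoints. This does not help: a week-26 value used as an outcome does not condition the week-52 contrast.

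**Conclusion.** The concern holds for ABC, TAND-SQ, CBCL/ABCL/ASR, PROMIS and the behaviour ratings on CGI-S/CareGI-S. For these, the week-52 contrast as specified is biased whenever period-1 behavioural response influences the choice after week 26. The bias probably favours CBD, reverses if improvers stop, and vanishes if behaviour plays no part.

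Under the assumptions of step 3, the false difference is about 0.13 to 0.56 SD and nominal significance occurs in about 7% to 48% of trials, against a nominal 5%. Stronger correlation between behavioural and seizure response makes it smaller; the alternative data model in step 4 makes it larger. These figures show what the plan permits and do not predict the result.

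This should be fixed, as a cheap improvement to a conditional, nominal, secondary contrast.

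**What to change.** - In the week-52 CBD versus SoC model, add the week-26 value of the same endpoint as a covariate beside its baseline value, for every behavioural and global endpoint assessed at week 52. Change from baseline may then stay as the outcome.
- Describe the result as an adjusted association between period-2 treatment and outcome, and drop the term treatment effect.
- Optionally add a measure of period-1 tolerability to the propensity score. With about 15 participants on SoC the score supports few covariates, so direct adjustment for the week-26 endpoint value comes first.

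**Cost.** One degree of freedom per model, a wording change, and the loss of participants without a week-26 value. That loss should be small, because the arms form only after the week-26 review and the Sample size section already counts a participant as evaluable for an endpoint only with baseline and week-26 assessments. No new endpoint assessment is needed. Confounding by factors that week-26 scores do not capture remains, so the causal disclaimer should stay.
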